#### **5.2 Evaluation**

As bed bathing is performed in all patients and in a standardized manner, we will evaluate the potential effects of music during the morning bed bath. Evaluation may also be performed during bedside surgical dressing.

#### **5.3 Music intervention**

In the intervention group, patients will be exposed to music during the morning bed bath, using headphones connected to an MP3 converter via a Bluetooth connection. The same selection of passages by Mozart will be used in all patients. The music will start at the same time as the bed bath and continued throughout the bath and for 30 minutes after the end of the batch. Sound intensity will do not exceed 60 decibels.

#### **5.4 Common modalities in both groups**

BPS scores will be determined by a nurse, who will not be involved in providing the bath. The BPS score will be determined just before the bath; at completion of the bath; and 30, 60, and 120 minutes after the end of the bath. During the bath, the BPS score will be assessed in cases of variations of BPS score  $\geq 5$ . Total length of the bath will be recorded. All patients will receive analgesia and sedation as needed, according to the standard protocol in our unit, which involves various titrated combinations of midazolam, propofol, morphine, and/or sufentanil.

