#### **3.3. Primary outcome**

Total length of pain exposure (minutes) to a BPS score over or equal to 5 divided by total length of nursing procedure

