## **4. Conception of the study**

### **4.1 Study design**

A prospective, interventional, comparative, single center study.

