### **4.2 Sample size**

This is a pilot study, whose purpose is to obtain preliminary data and for which it is not possible to calculate a study sample size. The number of patients to be included was fixed at 60, ie 30 patients in each group (morning bed bathing and wound care with and without music).

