### **5. Intervention**

#### **5.1 Modalities of enrolment**

In this study, eligible patients will be consecutively included. The first 30 patients will be included in the control group and the next 30 patients in the intervention group.

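### The nurse who scores the BPS is separate from the bath team but not blinded: headphones worn only by music patients and the 30-then-30 enrolment order both reveal the group

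*Protocol*

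**What the plan says.** Section 5.4 of the protocol assigns the ratings in both groups as follows: "BPS scores will be determined by a nurse, who will not be involved in providing the bath". It lists scores just before the bath, at its completion, and 30, 60 and 120 minutes later. Within the bath there is no fixed interval: "During the bath, the BPS score will be assessed in cases of variations of BPS score" of 5 or more.

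Section 5.3 describes the equipment for one group only: "In the intervention group, patients will be exposed to music during the morning bed bath, using headphones connected to an MP3 converter via a Bluetooth" link. Music starts with the bath and runs until 30 minutes after it ends. No headphones are described for controls.

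Section 5.1 sets the allocation: "The first 30 patients will be included in the control group and the next 30 patients in the intervention group".

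Section 3.3 defines the primary outcome: "Total length of pain exposure (minutes) to a BPS score over or equal to 5 divided by total length of nursing procedure". The secondary outcome in 3.4 uses the same ratings, as time at the maximal score.

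Section 4.1 describes the design as "A prospective, interventional, comparative, single center study". Neither there nor elsewhere does the protocol mention blinding or randomisation. The summary in section 1 repeats these arrangements.

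**The concern.** Keeping the scorer out of the bath means that she does not rate the effect of her own care. It does not stop her from knowing the group, and two features of the plan tell her.

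That matters for this outcome in particular. The BPS is a behavioural rating made by an observer, and the primary outcome cuts it at one value. A minute rated 4 instead of 5 drops out of the numerator entirely. There is a second route as well. Because scoring during the bath depends on a change being noticed, the same informed observer decides when a painful period opens and closes. Expectation could act on the rating and on its timing. Both would push the same way if the scorer expects music to help.

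At stake is whether a difference between groups can be read as an analgesic effect of music, which is the question in the title. The trial is a pilot meant to give preliminary data, so a biased estimate would be carried into whatever is planned next.

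**Working it through.** The protocol gives no derived figure to reproduce: "The number of patients to be included was fixed at 60, ie 30 patients in each group", without an effect size, SD or power. The check is therefore mainly one of reasoning, with two illustrations of size.

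**Step 1. When are the headphones in view?**

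| Score | Headphones described as in use (music group) |
|---|---|
| Just before the bath | No; music starts with the bath |
| During the bath | Yes |
| At completion | Yes |
| 30 minutes after | Up to this point, when the music ends |
| 60 and 120 minutes after | No |

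Both outcomes accrue over the nursing procedure, which lies within the period when the headphones are in view.

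**Step 2. Can the group be known without the headphones?** Under 5.1, patients 1 to 30 are controls and patients 31 to 60 receive music. Anyone who knows the inclusion number or the study phase can name the group for 30 + 30 = 60 of 60 patients.

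**Step 3. What does each remedy achieve?**
- Matching headphones with the 30-then-30 order kept: still 60 of 60 for anyone who knows the phase, because silent headphones in the first phase are known to mean control.
- Concealed 1:1 random allocation without matching headphones: the headphones still show the group during the bath.
- Both together, if masking works: a guess is right about 50% of the time.

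**Step 4. Illustration of the consequence.** Inputs from the protocol are n = 30 per group (4.2) and two-sided alpha = 0.05 (section 8). The assumed input is a rating bias of b SD with no true effect. With a normal approximation:

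SE = sqrt(2/30) = 0.258 SD; false-positive rate = Φ(b/SE − 1.96) + Φ(−b/SE − 1.96)

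| Assumed bias b (SD) | False-positive rate |
|---|---|
| 0 | 5.0% |
| 0.1 | 6.7% |
| 0.2 | 12.1% |
| 0.3 | 21.3% |
| 0.5 | 49.1% |

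For b = 0.2: 0.2/0.258 = 0.775, so Φ(−1.185) + Φ(−2.735) = 0.118 + 0.003 = 0.121.

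**Step 5. The same idea on the scale of the outcome.** Suppose that 30% to 60% of the time at BPS 5 or more is spent at exactly 5, and that the scorer records 4 for 20% to 30% of those minutes in the music group. Recorded exposure then falls by 0.30 × 0.20 = 6% to 0.60 × 0.30 = 18% in relative terms, with no true effect. Neither range comes from the protocol.

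**The case against.** The protocol never claims blinding, calls itself a pilot, and already keeps the scorer apart from the carers. Nothing in it contradicts itself here; this is a design limitation that is partly mitigated. That is fair, and it limits how strongly the point should be put. It does not remove the point, because separation is not masking and the protocol still plans tests at the 0.05 level.

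Four stronger readings are tempting, and the document does not support them.

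- A reader might infer that matching headphones would by themselves remove most of the bias. They would not, since the enrolment order in 5.1 reveals the group by study phase.
- A reader might infer that the headphones mark the group at every score. Section 5.3 ties the music to the bath and the following 30 minutes. Nothing says that headphones are worn at the pre-bath, 60-minute or 120-minute scores.
- A reader might add that headphones in one group mix the effect of music with that of reduced ambient noise. No part of the protocol says that the headphones reduce noise. Comparing care with and without music, delivered as a nursing intervention, is a legitimate question.
- A reader might take the 6% to 18%, or the inflated error rates, as the size of the bias. They follow entirely from assumed inputs.

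It is also right that the remedy is not free-standing: it requires a change to the allocation.

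**Conclusion.** The point holds in this form: the scorer is not blinded, the headphones and the sequential allocation each reveal the group, and the primary outcome is an observer-rated threshold measure whose scoring during the bath depends on what that observer notices. A difference between groups could partly reflect the scorer's expectation.

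The size cannot be derived, because the protocol gives no SD, expected exposure or distribution of scores around 5. The illustrations show only that a modest bias would matter with 30 per group, and they rest on the assumed bias and a normal approximation. The conclusion about unblinding needs neither; it assumes only that the scorer sees the patient or knows the study phase. The change is worth making, but the protocol contains no misstatement on this point.

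**What to change.** Make the changes as a package, because no single part is enough.

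1. **Section 5.1:** replace the 30-then-30 sequence with concealed 1:1 random allocation. The rest depends on this.
2. **Section 5.3:** place the same headphones and player on all patients during the bath and for the 30 minutes after it, silent in controls. An existing team member other than the scorer starts the track or the silence.
3. **Section 5.4:** state that the scoring nurse is not told the group, and that she records a guess of the group after the last score. The guesses show how well the masking worked.

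**Cost.** The headphones and player are those already planned, and no extra staff are needed. The larger change is in 5.1, where a two-phase consecutive design becomes a randomised one. The control condition becomes headphones without music rather than usual care, and the protocol must describe it so. Blinding may remain imperfect: sound can leak, and the bathing team, one of whom may know the group, can give cues to a scorer nearby.

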### **3.4. Secondary outcomes**

Total length of exposure to the maximal BPS score (over or equal to 5) among total length of nursing procedure

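### BPS during the bath is scored only when the BPS itself triggers it, with no timing rule, so both outcomes depend on when an observer not stated to be masked chooses to score

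*Protocol*

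**What the plan says.** The primary outcome (Protocol 3.3) is "Total length of pain exposure (minutes) to a BPS score over or equal to 5 divided by total length of nursing procedure". The secondary outcome (3.4) is "Total length of exposure to the maximal BPS score (over or equal to 5) among total length of nursing procedure". Both numerators are durations within the procedure.

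The measurement schedule is in 5.4: "The BPS score will be determined just before the bath; at completion of the bath; and 30, 60, and 120 minutes after the end", with the last three times counted from when the bath finishes. For the bath itself, the same section says "During the bath, the BPS score will be assessed in cases of variations of BPS score", followed by the threshold ≥ 5. The Intervention row of the summary (section 1) repeats the rule.

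On who scores, 5.4 says "BPS scores will be determined by a nurse, who will not be involved in providing the bath". Masking of this nurse to group is not described. Music is delivered "using headphones connected to an MP3 converter via a Bluetooth connection" (5.3), and no headphones are described for controls. Enrolment is sequential (5.1): "The first 30 patients will be included in the control group and the next 30 patients in the intervention group".

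Section 6 lists total minutes at a BPS of 5 or more, and total minutes at the maximal BPS, as items collected prospectively at the bedside on a standardized form. It gives no interval and no start or stop rule for either.

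**The concern.** A variation in the BPS is known only by scoring the BPS, so the in-bath rule presupposes the measurement it is meant to prompt. In practice the nurse has to form an impression that pain has changed and then score it. A duration also needs a start and an end, and the protocol does not say how either is fixed.

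Two things are at stake. The first is the comparison, which section 8 tests two-sided at 0.05: if readiness to score differs between control and music patients, a difference can appear without any effect of music. The second is the preliminary data that section 4.2 gives as the purpose of this pilot: if episodes are missed or badly timed to the same degree in both groups, the comparison may survive, but the exposure estimates will be wrong. A statistical analysis plan cannot repair either problem, because it cannot recover scores that were never taken or times that were never noted.

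**Working it through.** **1. No stated figure to reproduce.** The protocol gives no bath length, expected exposure or power calculation. The only arithmetic is 30 + 30 = 60 patients (4.2), which agrees.

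**2. What the outcomes need against what is collected.**

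| Needed for 3.3 and 3.4 | Provided in 1, 5.4 and 6 |
|---|---|
| BPS level over the whole procedure | Scheduled scores just before and at completion; none scheduled in between |
| Time at which BPS reaches 5 | Trigger expressed in the BPS itself; no clock time required |
| Time at which BPS falls below 5 | No rule |
| Time at the maximal BPS | Named as a data item; no timing rule, although the maximum is known only once the procedure is over |

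**3. Direction of error.** Take an assumed 30-minute bath with one assumed 2-minute episode starting halfway, at minute 15.
- True exposure: 2/30 = 6.7%.
- Episode not noticed and recorded as no pain: 0/30 = 0%.
- Episode scored on onset, its end not noted, and the score carried forward to completion: (30 − 15)/30 = 50%.

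The text excludes neither error, so it does not fix the direction.

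**4. Hypothetical size under differential detection.** Two simulations had 30 patients per group, no true music effect and a two-sided Mann-Whitney test at 0.05. Each painful episode was recorded in full with a detection probability p, and otherwise counted as no pain. Bath length, pain pattern and p are assumptions, not protocol figures. In expectation,

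recorded proportion = true proportion × p.

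*Simulation A:* 20-minute bath, true mean exposure 28% (SD 19 points), 3000 trials.

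| p control | p music | Recorded means | Rejection |
|---|---|---|---|
| 0.90 | 0.75 | 24.9% v 20.8% | 16% |
| 0.90 | 0.60 | – | 49% |

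*Simulation B:* 30-minute bath, episodes averaging 2 minutes, gaps averaging 5 minutes, true mean exposure about 0.272, 2000 trials per row.

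| p control | p music | Recorded means | Rejection |
|---|---|---|---|
| 1.0 | 1.0 | 0.272 v 0.273 | 4.5% |
| 0.9 | 0.9 | 0.245 v 0.245 | 4.5% |
| 0.9 | 0.8 | 0.245 v 0.219 | 12% |
| 0.9 | 0.7 | 0.245 v 0.190 | 38% |
| 0.9 | 0.6 | 0.245 v 0.163 | 69% |
| 0.9 | 0.5 | 0.246 v 0.136 | 93% |

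Check of the formula in B: 0.272 × 0.9 = 0.245 and 0.272 × 0.6 = 0.163, as simulated.

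**5. Reading.** With equal detection the test keeps its level, and only the estimate shifts. Every excess rejection comes from the assumed difference in p. At the same 0.9 v 0.6, the two models give 49% and 69%, so the percentages belong to the assumptions and not to this trial.

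**The case against.** The strongest defence is that a dedicated observer was intended. A nurse who does not give the bath does the scoring, and section 6 has pain minutes recorded at the bedside on a form. Taken together, these fit someone watching throughout and logging each change at or above 5. That is event recording, a sound way to measure duration and not circular. This reading is plausible and would give usable data. The protocol does not state it, however, and gives no onset or offset rule. If it was meant, it needs to be written down.

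Four stronger readings are tempting, and the documents do not support them.

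- *The trigger means a change of at least 5 points, so a rise from 4 to 8 would never be scored.* Elsewhere in sections 1, 3.3, 3.4 and 6, 5 is a score level. The point-change reading is strained.
- *Pain duration is not measured at all.* Section 6 names it as a recorded item. What is missing is the way it is timed.
- *Exposure is necessarily underestimated, because missed episodes count as no pain.* The protocol does not say how unscored time is treated, and carrying a score forward would overestimate.
- *The simulations show the trial's false-positive rate.* They show only what assumed differences in detection would do. The protocol gives no basis for any particular detection rate.

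It is also fair to say that unmasked observation and sequential allocation are design issues in their own right. They would remain with perfect timing: an observer who sees the headphones can still score 4 instead of 5.

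**Conclusion.** The point holds in this form: the in-bath scoring rule is defined by the score it should prompt, and no rule times when the BPS reaches or falls below 5 or how long the maximum lasts. As written, neither the primary nor the secondary outcome can be obtained reproducibly. Pilot status does not excuse this, since preliminary values of exactly these quantities are the purpose of the study.

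The size and direction of the error cannot be determined from the protocol. As a hypothetical, with no true effect and the assumed bath and pain patterns above, rejection is near nominal when detection is equal, about 12–16% at modest differences (0.9 v 0.8 or 0.75) and 49–69% at 0.9 v 0.6. A difference between groups is possible because the observer is not stated to be masked, the headphones are visible and the groups are enrolled one after the other. That it would occur is not shown.

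**What to change.** **Sections 5.4 and 1 (Intervention row).** Replace the triggered rule. In both groups, the nurse who does not give the bath scores the BPS from start to end of the procedure at a fixed short interval, for example every minute. This nurse also records the clock time of each observed crossing of BPS 5, in either direction, and of each change in the maximal score. The clock times matter because a grid alone loses short peaks: a 2-minute grid in an assumed 20-minute bath gives only about 20/2 = 10 readings.

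**Sections 3.3 and 3.4.** Define pain time (BPS ≥ 5) and time at the maximal BPS from these timed records. Keep the existing denominator, the total length of the nursing procedure, so that the definitions also cover the bedside surgical dressings allowed in 5.2.

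**Section 6.** Add the timed grid and clock times to the standardized form, so that the total minutes are derived from records and not entered as a summary.

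**Cost.** More entries: at one per minute, about 20 to 30 for a bath of the assumed 20 to 30 minutes. Extra staff should not be needed if the scoring nurse is already there throughout, but the protocol only implies this and should state it.

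**Limit.** A fixed schedule takes away the choice of when to score, not the judgement of what to score. It reduces bias from unmasked scoring without removing it, and it does nothing about sequential enrolment.

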#### **6. Data collection**

Demographic and clinical data will be collected prospectively at the bedside on a standardized form. Demographics data: age, gender, reason for ICU admission (medical, emergency surgery, scheduled surgery), comorbidities, reason for mechanical ventilation, ICU length of stay before inclusion. Patients characteristics at inclusion: presence of tracheotomy, chest tubes, central venous catheter, arterial line, gastric tube, surgical drain tube. Nursing care characteristics will be assessed in both groups at baseline; during; and 30, 60, and 120 minutes after the end of the evaluated nursing care. Total length of nursing procedure will be recorded. Data related to pain assessment: Total length of pain exposure (minutes) to a BPS score over or equal to 5; and total length of exposure to the maximal BPS score (over or equal to 5).

## **7. Ethic and regulary considerations**

Our local ethics committee approved this prospective pilot study (*Comité de Protection des Personnes, Paris – Ile de France VI*, 5 October 2012, #12044). Written informed consent from a relative or surrogate will be obtained for each participant before study inclusion and, whenever possible, from the patients before ICU discharge. This study will be performed in compliance with the ethical standards of the institutional and national research committees and with the 1964 Declaration of Helsinki and its later amendments.

## **8. Statistics**

Quantitative parameters will be described as median (interquartile range [IQR]) and qualitative parameters as number (%). Categorical variables will be compared using Fisher's exact test and continuous variables using the t test or Mann Whitney or Wilcoxon tests depending to sampling distribution. All tests will be two-tailed at the 0.05 significance level with a two-sided hypothesis.

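### Section 8 compares groups formed by order of entry only by unadjusted tests at 0.05; at 30 versus 30 a non-significant baseline test is not evidence of balance, and case mix is left unaddressed

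*Protocol*

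**What the plan says.** Allocation is by order of entry (Protocol, section 5.1): "The first 30 patients will be included in the control group and the next 30 patients in the intervention group". The size is set by decision, with no calculation (section 4.2): "The number of patients to be included was fixed at 60, ie 30 patients in each group".

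Section 8 is the whole of the stated analysis. It first plans medians with interquartile ranges, and counts with percentages. It then gives the tests. For one type of variable the rule is "Categorical variables will be compared using Fisher's exact test". For the other type it offers a choice that depends on the distribution: "continuous variables using the t test or Mann Whitney or Wilcoxon tests depending to sampling distribution". The level is common to all of them: "All tests will be two-tailed at the 0.05 significance level with a two-sided hypothesis". The section does not say which variables are tested, and it names no adjustment.

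The primary outcome (section 3.3) is a ratio of durations: "Total length of pain exposure (minutes) to a BPS score over or equal to 5 divided by total length of nursing procedure". The secondary outcome (section 3.4) is also a ratio of durations. The categorical variables that the protocol names are mostly baseline items in section 6: several among "age, gender, reason for ICU admission (medical, emergency surgery, scheduled surgery), comorbidities, reason for mechanical ventilation, ICU length of stay before inclusion", and all of "presence of tracheotomy, chest tubes, central venous catheter, arterial line, gastric tube, surgical drain tube".

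**The concern.** Nothing in the design balances two groups recruited one after the other. They can differ in surgical case mix or in the number of patients with drains, and the protocol's own rationale (section 2) counts drain removal, post-operative care and wound care among the causes of pain in intensive care. The bias from such a difference depends on how large it is in these 60 patients and how strongly the factor affects pain. A p-value measures neither.

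Because the testing rule is unrestricted, it covers the baseline items. At this sample size a sizeable imbalance will often be non-significant. Section 8 then compares pain between the groups without using any of the characteristics that section 6 collects. What is at stake is whether a difference in pain exposure, or its absence, can be attributed to music.

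**Working it through.** **Inputs from the protocol.** 30 per group (section 4.2); two-sided 0.05, Fisher's exact test for categorical variables and t or rank tests for continuous ones (section 8). The protocol gives no power, rate or standard deviation, so there is no figure of its own to reproduce. The imbalances below are assumptions, shown as a range.

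**Step 1: categorical items.** Exact power is the sum, over all pairs (a, b) from 0 to 30, of Bin(a; 30, p1) × Bin(b; 30, p2), counting only pairs whose two-sided Fisher p is at most 0.05.

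| True proportions | Gap (points) | Power | Missed |
|---|---|---|---|
| 10% v 20% | 10 | 9.6% | 90.4% |
| 50% v 60% | 10 | 7.7% | 92.3% |
| 10% v 30% | 20 | 37.2% | 62.8% |
| 20% v 40% | 20 | 29.8% | 70.2% |
| 30% v 50% | 20 | 25.9% | 74.1% |
| 40% v 60% | 20 | 25.7% | 74.3% |
| 10% v 40% | 30 | 70.5% | 29.5% |
| 20% v 50% | 30 | 59.6% | 40.4% |
| 30% v 60% | 30 | 56.1% | 43.9% |
| 20% v 60% | 40 | 85.1% | 14.9% |

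Power of 80% needs a gap of about 34 to 38 points (10% v 44%; 20% v 58%; 30% v 68%).

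**Step 2: continuous items.** Two-sample t test with 58 degrees of freedom and non-centrality d × √(30/2). At d = 0.5 this is 0.5 × 3.873 = 1.94, against a critical value of 2.00, and power is 47.8%. At d = 0.3 power is 20.8%, at 0.6 it is 62.8%, and at 0.7 it is 76.0%. Power of 80% needs d = 0.74. An observed difference below 2.00 × √(2/30) = 0.52 SD cannot be significant.

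**Step 3: observed tables.** This step needs no assumed population rate.

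- 6/30 v 12/30 gives p = 0.158. The standardised difference is 0.20 / √((0.16 + 0.24)/2) = 0.45.
- 6/30 v 14/30 (20% v 47%) gives p = 0.054. Significance is first reached at 15/30, with p = 0.029.
- 9/30 v 17/30 (30% v 57%) gives p = 0.067. Significance is first reached at 18/30, with p = 0.037.

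Imbalances of about 27 points in the sample can therefore be non-significant.

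**Step 4: effect on the primary comparison.** For one factor, bias = imbalance × difference in outcome between patients with and without it. Assume that patients with a drain spend 10 to 40 percentage points more of the procedure at a BPS of 5 or above; the protocol gives no such figure. A 20-point imbalance in drains then shifts the group difference by 0.20 × 10 = 2 to 0.20 × 40 = 8 points. The direction depends on which group has more drains.

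**The case against.** **Section 8 does not mention a baseline table.** This is true. That baseline items would be tested is an inference from an unrestricted rule and the variable list in section 6. A reader might go further and infer that a non-significant table is planned as proof of comparability. No sentence in the protocol says so.

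**Fisher's test may have other uses.** This also stands. The secondary objective (section 3.2) speaks of the occurrence of peak pain, which could be read as yes or no; the nursing care characteristics in section 6 may be categorical; and section 5.2 allows two kinds of procedure. The test would fall mainly on patient characteristics, but not necessarily on them alone.

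**The size of any imbalance will be visible.** The planned counts, percentages and medians would show 20% against 40% directly, so the p-value is not the only information on balance. Replacing p-values with standardised differences is mostly presentation and would not justify this point alone.

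**The tests are not blind to every imbalance.** At 30 points Fisher's test detects 56–71%, and at 0.7 SD the t test detects 76%. A claim that most imbalances are missed holds only up to about 20 points, or just under 0.5 SD.

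**A SAP may add adjustment.** It may, and silence on such details is not the complaint. The complaint is what section 8 fixes: unadjusted tests, unrestricted in scope, for a sequential comparison.

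**Sequential allocation is the root problem.** Agreed. Dropping baseline tests removes no bias, and adjustment for measured factors removes only part of it.

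**Conclusion.** The point holds as a limited criticism of the stated analysis. Groups formed by order of entry are compared by unadjusted tests alone, and those tests, as worded, extend to baseline items. At 30 versus 30 they give power of 26–37% for 20-point imbalances, 56–71% for 30-point ones and 48% at 0.5 SD, so a non-significant result cannot support a claim of balance. A case-mix difference may bias the pain comparison, and section 8 does nothing about it.

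The power figures follow exactly from the group size and the level, given the assumed imbalances. The 2 to 8 points of bias illustrates one factor under an assumed effect. It is not an estimate for this trial, and the protocol gives no expected difference or SD to set it against. The protocol does not show that an imbalance will occur or that p-values will be misread. The improvement that matters is the pre-chosen adjusted analysis.

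**What to change.** In section 8:

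1. Limit hypothesis tests to the primary and secondary outcomes.
2. Describe the section 6 baseline characteristics by group and give the size of each difference, for example as a standardised difference. State that p-values are not used to judge comparability.
3. Add one sensitivity analysis of the primary outcome, adjusted for a small set of covariates named in advance: for example surgical versus medical admission, and presence of a surgical drain or chest tube. Keep the set whatever imbalance is observed, and report the result beside the unadjusted one. Name the model in advance too, since the outcome is a ratio bounded by 0 and 1.
4. State that the adjusted result does not deal with calendar-period or unmeasured differences, so conclusions about music remain cautious.

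The cost is a few sentences and one regression on data already to be collected, with no extra patients. It uses about two degrees of freedom in 60 patients. The two example covariates probably overlap, which would cost some precision, and the final choice needs clinical judgement before the data are seen.
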